### Data collection

Once ethics approval is received at the participating sites, collection of pre-implementation data will begin. Data will be collected three times per day (in the morning, at lunch, and in the afternoon) and two days each week (excluding holidays and weekends). This data collection will occur over three phases: pre-implementation (10 weeks or 20 assessment days), implementation (8 weeks or 16 assessment days), and post-implementation (20 weeks or 40 assessment days) (Table 2). In order to detect a 10% decrease for the patients being in bed after the intervention, based on a power of 0.8 and type I error of 0.05, correlation for AR(1) of 0.4 and proportion of patients being in bed before the intervention at 66%, the required number of data collection points is 40.

Baseline data will be collected on eligible patients including age, gender, place of residence prior to admission, admitting diagnosis, and functional status prior to admission from the chart. This information will be collected retrospectively from chart review.

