### Analysis

#### Quantitative analysis

The interrupted time series design will be used as it is more robust than a simple before-after study design. The primary outcome is the proportion of patients aged 65 and older who are mobilized three or more times daily during the audit. Mobilization is defined as not being in bed. The primary analysis will compare the proportion of inpatients aged 65 years and older who were mobilized in the pre-, during and post-intervention periods. We will also perform subgroup analyses across the different participating hospitals to provide site-specific data. The unit of experimentation will be based on multiple temporal assessments. For the primary outcome, 20 consecutive time points over 10 weeks will be used to create a pre-intervention model. To evaluate whether this pre-intervention model adequately describes the baseline, time series models will also be estimated for the entire 76 time points (pre- and post-intervention). We anticipate that each site will obtain data on 35 to 45 patients per audit. Segmented linear regression models will be performed to examine the impact of the intervention on the primary outcomes [34]. The initial time series regression model included terms estimating changes in the level and trend of outcome rates after intervention, in addition to the constant term, and the term estimating changes in baseline trend over time. Durbin’s alternative test [35] will be used to examine for the presence of serial autocorrelation among the observations, and models will be corrected for autocorrelation as required using the Cochrane-Orcutt methodology [36]. All statistical analyses will be conducted using SAS version 10.0, and statistical significance will be set at p <0.05.

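### The stated rule for autocorrelation (test first, then Cochrane-Orcutt) gives a false-positive rate of about 10% to 11% per coefficient at the plan's own AR(1) of 0.4, not 5%

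*Protocol article*

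**What the plan says.** In the protocol article, the Data collection section derives the number of time points "based on a power of 0.8 and type I error of 0.05, correlation for AR(1) of 0.4", with 66% of patients in bed at baseline and a 10% decrease to detect. The required number is given as 40.

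The Quantitative analysis section then sets out a segmented linear regression with a constant, a baseline trend, a change in level and a change in trend. There are 20 pre-intervention points and 76 points in all. Durbin's alternative test comes first, and then "models will be corrected for autocorrelation as required using the Cochrane-Orcutt methodology". The threshold is stated once: "statistical significance will be set at p <0.05".

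On the target of the analysis, the same section says: "The primary analysis will compare the proportion of inpatients aged 65 years and older who were mobilized in the pre-, during and post-intervention periods". It does not say which coefficient or contrast answers the primary question.

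**The concern.** The plan takes substantial autocorrelation as given when it sizes the study, but at analysis it corrects for it only when a test finds it. In a series of this length the test sometimes misses real autocorrelation, and ordinary least squares is then used with standard errors that are too small. When the test does find it, Cochrane-Orcutt estimates the correlation from residuals. In a short series with four regression terms that estimate is too low, so the standard errors remain too small.

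The study has no control group, and the outcome observers are aware of the phase. The causal claim therefore leans on this model. If its real error rate is about twice the nominal one, the p-values and confidence intervals for the main result look firmer than they are. Site-specific analyses under the same rule would share the fault.

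**Working it through.** **1. The plan's own figure.** The inputs, all from Data collection and Quantitative analysis, are 66% in bed, a 10% decrease (taken here as absolute, to 56%), two-sided 0.05, power 0.80, AR(1) 0.4, and 35 to 45 patients per point.

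Points per phase = (1.96 + 0.84)² × [0.66×0.34 + 0.56×0.44]/m ÷ 0.10² × (1 + 0.4)/(1 − 0.4)

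With m = 45: 7.85 × 0.4708/45 ÷ 0.01 = 8.21, and 8.21 × 2.33 = 19.2. That rounds up to 20 per phase, or 40 in total. With m = 40 the total is 44, and with m = 35 it is 50. The stated 40 is thus reproduced at 45 patients per point. Without the AR(1) factor it would be 2 × 9 = 18, so the correlation more than doubles the requirement. The plan clearly treats it as real.

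**2. Error rate of the planned procedure.** The model is

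Y(t) = b0 + b1·t + b2·I(t > T) + b3·(t − T)·I(t > T) + e(t), with e(t) = ρ·e(t−1) + u(t),

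with b2 = b3 = 0 and 76 points. Durbin's alternative test is run at 5%. Ordinary least squares is kept if it is not significant, and iterated Cochrane-Orcutt is used if it is. Each coefficient has a two-sided t test at 5%. There were 6,000 series per scenario, so the Monte Carlo standard error near 10% is √(0.1 × 0.9/6000) = 0.4 points.

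| ρ | Break after point | Durbin significant | Planned rule: level / trend | Cochrane-Orcutt always: level / trend | OLS always: level / trend |
|---|---|---|---|---|---|
| 0 | 20 | 7.1% | 5.6% / 5.7% | 6.9% / 6.8% | 5.1% / 5.2% |
| 0.2 | 20 | 19.9% | 8.5% / 9.5% | 6.8% / 7.5% | 9.4% / 10.6% |
| 0.2 | 36 | 19.9% | 9.4% / 9.5% | 7.3% / 7.5% | 10.5% / 11.0% |
| 0.4 | 20 | 78.0% | 9.7% / 10.0% | 8.2% / 8.4% | 17.8% / 19.0% |
| 0.4 | 36 | 76.9% | 9.8% / 11.0% | 8.2% / 9.4% | 18.6% / 20.8% |

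A separate simulation of 3,000 series at ρ = 0.4 with the break at 20 gave 10.8% / 9.8% for the planned rule and 9.0% / 8.2% for Cochrane-Orcutt always.

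**3. Where the excess comes from.** At ρ = 0.4 with the break at 20, the pre-test accounts for 9.7 − 8.2 = 1.5 points (level) and 10.0 − 8.4 = 1.6 points (trend). The estimator accounts for 8.2 − 5 = 3.2 and 8.4 − 5 = 3.4 points, about two thirds of the excess. The first point that Cochrane-Orcutt drops is not the reason: Prais-Winsten, which keeps it, gives 8.5% / 8.4% when always applied. With ρ known to be 0.4 the rates are 4.8% / 4.4%, so the fault lies in estimating ρ.

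**4. If either term could count.** At ρ = 0.4 the planned rule rejects on at least one of the two terms in 16.3% of series (break at 20) or 19.1% (break at 36). At ρ = 0.6 with the break at 36 it is 21.1%. Part of this is plain multiplicity: with ρ known to be 0.4 it is still 8.2%.

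**5. The alternative.** AR(1) was fitted by REML every time, with t or F tests on n − 4 degrees of freedom (8,000 series, ρ = 0.4, break at 20). The rates are level 6.4% and trend 5.5%. One fixed contrast, b2 + 36·b3 (the effect at point 56, the middle of the post-implementation period), gives 5.6%; the separate simulation gave 6.3%. A joint 2-df test of level and trend gives 6.9% and 7.1% in the same two simulations.

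**The case against.** The best defence is that the article condenses a fuller plan, which may name the decisive coefficient and handle multiplicity. That stands as far as it goes: the lack of a named term is not in itself an error. It does not cover the correction rule, which the article states.

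A reader might infer more than the text supports in three places.

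- **That the pre-test is the main culprit.** It is not. Durbin's test detects the correlation in about 77% of series at 0.4, and using Cochrane-Orcutt every time leaves most of the excess.
- **That the trial's false-positive rate is 16% or more.** That needs a rule by which a significant level or trend term alone proves success. The article neither states nor excludes such a rule, and part of the figure is ordinary two-coefficient multiplicity.
- **That the three-period sentence adds a crude before-after test.** It can equally be read as the aim that the segmented regression carries out. The section opens by preferring the time series design to a simple before-after study, and it describes no separate test of proportions.

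The simulation also rests on settings that the article does not give. Changing the pre-test moves the result little: a one-sided 5% test gives 8.9% / 9.6%, and a 20% threshold gives 8.3% / 9.1%. Leaving out the roll-out points (60 points) makes it worse, at 11.2% / 12.0%. The exact figure is therefore uncertain, but not the direction.

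**Conclusion.** The point holds for the stated correction rule. At the plan's own AR(1) of 0.4, the procedure rejects a true null in about 10% to 11% of series per coefficient, against a stated 5%; at 0.2 it is about 8% to 9.5%. The larger cause is Cochrane-Orcutt in a short series (about 8% to 10% on its own), and the pre-test adds about 1.5 to 2 points. If either term were allowed to decide, the rate would be about 16% to 19% at 0.4 and up to about 21% at 0.6, but this is conditional on a success rule that the article does not contain.

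The assumptions are one 76-point series, Gaussian AR(1) errors, a 5% pre-test, two-sided tests, and one break at point 20 (roll-out counted as after) or 36 (roll-out counted as before). The article does not say whether the series is pooled or by site.

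**What to change.** Three changes to the analysis text, made before the post-implementation data are analysed:

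1. Drop the pre-test. Fit the AR(1) error model by REML in every primary and site-specific analysis. Durbin's test may still be reported as a diagnostic. Dropping the pre-test but keeping Cochrane-Orcutt is not enough.
2. Name one model-based primary contrast, for example the effect against the projected baseline at the middle of the post-implementation period. A joint 2-df test is no better on error rate, and it can reject when level and trend move in opposite directions.
3. Report the level and trend changes as estimates with confidence intervals, and say that the pre, during and post comparison is carried out through this model.

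The change needs no new data and uses standard SAS procedures. Intervals will be slightly wider. The error rate will be close to 5% but not exactly 5%; a further small-sample correction to the degrees of freedom might help but was not checked here. Any contrast against a projected baseline also leans on a slope estimated from 20 points, which is a reason to report the component estimates beside it.

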#### Qualitative analysis

Content analysis of the transcripts will begin after the first completed focus group and will draw on grounded theory, although no theory will be developed [37].The goal of these interviews and the analysis of their content is to develop a synopsis of the understanding of the key domains of behavior change that need to be targeted on the various clinical units. Additional interview questions may be identified through this process; thus, post-implementation interviews will be modified as necessary. Analysis will be completed independently by two investigators. Written memos will be used to provide a record of the analytic process. The memos will capture the decisions and results of the analysis and help to develop propositions. Investigators will deliberately try to discount or disprove a conclusion drawn from the data. Reliability of the categories will be determined by the frequency or consistency with which they are indicated by participants in their interviews. All participants will be provided with a copy of the study report for their review and comments. Sampling will continue until no new themes are identified, and it is anticipated that approximately one to three focus groups will be conducted at each site. Analysis will be done using NVivo 10.

Content analysis of the staff and patient and/or family interviews will be done by two team members independently using the methods described above for the baseline focus groups. Sampling will be continued until no new themes are identified. It is anticipated that up to 10 interviews may be completed for each hospital.

### Study status

A launch meeting was held in 2012 with the participating teams in Toronto, Canada, and monthly phone calls are held for all participants to share experiences. All sites have completed their baseline data collection phase, and the tailored intervention is being rolled out at all sites. Approval has been received from the research ethics board at each of the participating hospitals.

## Discussion

This is the first large, multisite study to evaluate the impact of a multi-component KT strategy on rates of mobilization of older patients in hospital. Our implementation is framed by the KTA cycle [18], and the intervention is being adapted to the local context of the implementation site. The contextualization of the educational intervention will be informed by the focus group findings, which will reflect the unit characteristics, patient profile, staffing profile, and external environmental factors influencing the unit’s capacity for change. This unique feature renders our intervention approach more generalizable to multiple practice settings. It has also facilitated engagement of participants from multiple hospitals.

This study incorporates evidence-based success factors for quality improvement. First, we are ensuring that key stakeholders are engaged in all phases of the study. Our intervention is adapted to local context. Second, the education component of the intervention is reinforced through the use of enabling tools, coaching, and learning resources that are made available to all sites. Third, our intervention emphasizes the inclusion of all interprofessional team members to patient mobilization and does not rely on the contributions of a single individual or health profession [38].

There are several limitations to our study that should be acknowledged. First, the participating hospitals do not routinely collect data on mobilization of patients. Our primary outcome is based on three daily audits of patients being out of bed. Although we validated this measurement against a reference standard, it provides only an estimate of the total mobilization events that patients may undertake. We are not collecting data on evenings and weekends, when families tend to visit, since patients may be mobilized at a different rate during those times. One of the other goals of this project is to work with participating sites to develop a measure for assessing mobility that can be easily incorporated into paper and electronic medical records that are not too onerous for healthcare providers to use; its development will facilitate sustainability of this strategy. Second, the collection of outcome data (specifically, frequency of mobilization) by the research coordinator will not be blinded, and the research coordinator will be aware of the phase of implementation. We are, however, using standardized criteria for this outcome measure. Third, this project highlights the real world challenge of implementing evidence across multiple, different hospitals across a large province. There are always different initiatives underway at hospitals at the same time, all of which compete for hospital resources. We are vulnerable to the risk of initiative fatigue amongst frontline staff. We are using the local working groups to keep track of these other initiatives. Moreover, by allowing the local working groups to contextualize the mobilization intervention to their context, we anticipate alleviating some of this concern. Fourth, because this represents a real world implementation initiative, outcomes are subject to factors such as staff changes, infections outbreaks, and organizational restructuring. We will determine the impact of these confounders through our quantitative analysis as well as the qualitative component of our study.

Strengths of this initiative include the engagement of 93% of eligible academic institutions in Ontario, Canada, in this project. While inpatient medicine units are the initial targets of this strategy, efforts are already underway to scale this up across other units within the hospitals. Moreover, participating hospitals have expressed interest in using this provincial platform to implementing other strategies to optimize care of seniors in hospitals.

## Abbreviations

ADL: Activities of Daily Living; ALC: Alternate Level of Care; IADL: Instrumental Activities of Daily Living; KT: Knowledge Translation; KTA: Knowledge to Action Cycle; MOVE ON: Mobilization Of Vulnerable Elders in Ontario.
